#### Primary outcome

Quality of life is a widely recognized outcome, especially for chronic conditions. Indeed, recent German treatment guidelines for CHD patients recommend HRQoL as a primary outcomes goal [21], and we confirmed in a meeting with a local self-help group of cardiac patients that HRQoL coincides with their preference as an outcome. Furthermore, as there is not a single measure that assesses both our target conditions, CHD and distress, HRQoL can serve as a global measure of health. Therefore, our primary hypothesis is that compared to UC more patients in our TC intervention group will report a clinically meaningful improvement in HRQoL at 12-months.

The HeartQoL questionnaire [22] assesses HRQoL for patients with CHD, thus allowing to measure overall treatment response for our multimorbid population. It is a 14-item self-rating instrument that is proven reliable, valid, and responsive to change across various CHD populations, including the German version used in our study [23]. In the survey from de Smedt et al. [23], 7,449 patients completed the HeartQoL questionnaire with an excellent internal consistency for the global HeartQoL scale (Cronbach's alpha α = 0.92) and the physical subscale (α = 0.91), as well as good internal consistency for the emotional subscale (α = 0.87). We defined response to treatment as ≥ 50% increase in HeartQoL score (mean of 14 items scored 0–3, range 0–3) (i.e. (score_12 months_-score_baseline_)/(3-score_baseline_) ≥ 50%).

#### Secondary outcomes

Our main secondary outcome measure is a composite medical risk factor score based on current European Society of Cardiology (ESC) cardiovascular prevention guidelines [7]. Composite risk factor scores have been used in previous intervention research aiming to reduce risk factor burden (e.g., [11, 59]), and different ways for computing such scores (e.g. by weighting) have been proposed. Established scores such as the ESC SCORE [7] or the PROCAM score [24] have only been validated for individuals without known CHD, thus rendering all CHD patients as uniformly high risk. Therefore, Katon et al. [11] computed a composite measure by means of a multivariate scaled marginal model, where each outcome measure is scaled by its standard error. However, that model requires continuous data and does not seem to be feasible for the risk factors of interest in our trial. We will therefore use dichotomous data based on either presence vs. absence of a risk factor (e.g. smoking) or sufficient vs. insufficient control according to the ESC guideline. In accordance with Khaw et al. [25], our score will be computed as a sum (range 0–5) of the following most important, modifiable but often insufficiently controlled CHD risk factors: (1) Blood pressure > = 140/90 mmHg; (2) LDL-cholesterol > = 70 mg/dl; (3) current smoking; (4) HbA1c > = 7.0%; (5) physical inactivity as defined: < 150 min. of moderate or < 75 min. of vigorous physical activity per week.

Additional secondary endpoints include change in body mass index, medical events, health care utilization, and use of evidence-based medications. Disease-relevant health behaviors (e.g., physical activity, smoking, medication adherence) are assessed by self–report and objective measures (e.g. electronic activity trackers, cotinine in urine samples).

To further examine the impact of distress and mental health on patients’ outcomes, we will (a) explore patients’ change in HADS and PSS-4 scores across the time from hospitalization to end of study and (b) further assess their psychosocial risk and well-being with validated instruments (Table 4).HADSThe Hospital Anxiety and Depression Scale (HADS) [18, 26] assesses the severity of anxiety and depressive symptoms in physically ill patients. It is a self-rating instrument on a four-step Likert-Scale with 14 items, with higher scores signifying increased severity. The German version has been validated in several large samples of cardiac patients, mainly with coronary artery disease (e.g. [27–29]), is equivalent to the original English version [26], and norms are available for these patients. In a review of 747 studies using the HADS for different purposes, Bjelland et al. [30] found a mean Cronbach’s alpha of 0.82 for the subscale “anxiety” and of 0.83 for the subscale “depression”. For the inclusion criteria of elevated distress in our study, we define the relevant cut-off at a total score > 12 (range 0–21), which is expected to detect even mild symptomatology as this has already been shown to be prognostically relevant [18].PSS-4.The PSS-4 [31] is the short version of the well-established Perceived Stress Scale (PSS; [32]) that measures subjectively perceived distress. To assure equal validity in the German sample, the items are drawn from the German version of the PSS-10 [33], which yielded good psychometric properties equivalent to the original version. The items are answered on a 5-step frequency scale (range 0–16), where a higher score reflects the respondent’s perception that the demands exceed his/her ability to cope. For the present study we define a relevant screening cut-off score > 5 for defining elevated distress as we did in our pilot study [14].All outcomes will be assessed in all participants at baseline, month 12 (primary endpoint) and month 18. Selected self-report variables will additionally be assessed at month 6, and later until the end of the trial, i.e. after 24 months and 30 months in patients included during the early phase of the trial to test sustainability. We will track cardiac events and all-cause mortality by self-report, discharge notes, and death certificates, and document hospitalizations, numbers of outpatient visits, medication, and disability/return to work or early retirement for later cost-effectiveness analyses.

**Table 4 Tab4:** List of assessment instruments

Outcome	Measurement	Description	References
Social support	ENRICHD Social Support Inventory (ESSI)	5-Item scale to assess perceived emotional social support in CHD patients	[34, 35]
Health Literacy	European health literacy survey (HLS-EU-Q16)	16 items to assess knowledge, motivation and competences to access, understand, appraise, and apply health information; 3 subscales: health promotion, health treatment and prevention	[36, 37]
Attachment	Experience in close relationship instrument revised (ECR-RD8)	8 items on a 7-step match scale with two subscales: attachment-related anxiety and avoidance	[38, 39]
Resilience	Resilience Scale (RS-13)	13-item short version to measure the ability of mental resistance	[40, 41]
Demoralization	Demoralization scale (D-S)	24-Item questionnaire with 5 subscales: loss of meaning and purpose, dysphoria, disheartenment, helplessness and sense of failure	[42, 43]
Heart-related fears	Herzangstfragebogen (HAF-17)	17-Item questionnaire assessing behavior and emotions regarding heart-related symptoms, German adaptation of Cardiac Anxiety Questionnaire [44]	[44–46]
Angina symptoms	Seattle Angina Questionnaire (SAQ)	Assessing in 5 subscales: disease perception, physical limitation, angina frequency, angina stability and treatment satisfaction	[47, 48]
Medication adherence	Rief Adherence Index (RAI)	Describes frequency of their general past and present behaviors concerning medication intake as a percentage range on a five-stage Likert scale	[49]
Therapeutic alliance	Working Alliance Inventory—short revised (WAI-SR-P)	Measures the therapeutic alliance between patient and therapist from patient view. We use to measure the alliance with NCM in TC group. 12-items assess 3 subscales: binding, process, goals	[50, 51]
Physical activity	International Physical Activity Questionnaire (IPAQ-7)	7-Item to self-record hours and days of various activities with strenuous or moderate physical activity over7-day period	[52]
Personality functioning	Operationalized Psychodynamic Diagnosis—Structure Questionnaire short form (OPD-SFK)	12-Items assessing elements of personality structure	[53, 54]
Treatment satisfaction	Purpose-designed questions	Questions about overall treatment satisfaction, satisfaction with treatment of heart disease, satisfaction with treatment of distress	

### Trial status

Prescreening for the TEACH Trial has started in August 2020 and enrollment in the main trial has started in November, 2020.

## Data safety monitoring

An independent Data Safety Monitoring Committee (DSMC) reviews a defined data set in regular intervals and evaluates whether patient safety is ensured and whether the conduct of the trial complies with ethical requirements. Regular on-site monitoring by the UMG Clinical Trials Unit ensures compliance of study conduct with all applicable regulatory and ethical standards. The work of the DSMC is governed by a DSMC charter.

Furthermore, the study coordinating team will generate up-to-date administrative reports by the data management system to monitor: (1) trial enrollment by study center; (2) NCMs’ caseloads; (3) rates of follow-up assessments; (4) missed study assessments so that patients may be recontacted; (5) patients’ clinical status for data safety monitoring purposes; and (6) potential protocol deviations that the study investigators review at staff meetings as appropriate.

## Adverse events

Our blinded assessors inquire routinely about any adverse events (e.g. emergency room visits, hospitalizations, mental health visits) participants may have experienced since their past assessment. Since TEACH does not test any medicinal product or medical device, we decided to define attempted suicide, acute coronary syndrome, or death as serious adverse events of special interest requiring immediate notification of the coordinating investigator. Adverse events reported during care management are also documented.

In case the participant’s adverse event warrants medical attention, the assessors and NCMs will follow our standard operating procedures to initiate emergency care, to encourage participants to seek professional help, or to provide information about local emergency care or mental health resources.

All severe adverse events of special interest are reviewed by the coordinating investigator and reported to the DSMC.

An insurance will cover any accidents occurring to patients while attending scheduled trial visits.

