Starting with existing educational materials developed for our pilot study, we also provide a patient website with relevant audiovisual health information and regularly featured tips in support of behavioral change and stress reduction that is open to all participants and their family members. Furthermore, in a password-protected internet chat room for intervention participants only we offer weekly moderated text chats with an NCM, psychologist, or TC Team (TCT) member to obtain emotional support and learn from other patients’ experiences. At the end of each weekly session, we close the chat function, but all chats remain accessible to intervention participants in read-only mode. Participants are advised to choose nicknames and not disclose any identifiable information, which we will monitor during the chats. To further enhance the TC support, we send individualized text messages and recommendations for freely available mobile applications to remind patients of desired activities (such as exercising, taking medications, etc.) and encourage adherence to the treatment plan.

During each patient contact NCMs enter all information into our electronic patient registry (EPR) that will also guide the NCM through the contacts and prompt for relevant questions based on our manual. Based on own experiences from the U.S.A. ([name]) we programed the EPR so that NCMs can easily sort their patient panel by: last contact, symptom level, risk factors, and goal progression, and will be alerted to treatment gaps or deterioration. During the first 3–4 months of the intervention phase, NCMs contact patients twice a month for typically 30 min on average, after which contacts are once a month, unless different intervals are indicated.

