### Follow-up assessments and outcomes

At 12- (end of treatment) and 18-months after randomization participants are invited to come to their recruitment center, where a study physician and a study assessor blinded to participants’ randomization status administer the medical and psychometric assessment batteries. All patients are followed for a minimum of 18 months, 6 months after the completion of our TC, in order to document sustainability of our intervention. In addition, centrally located, blinded assessors will administer self-report psychometric and medical questionnaires via telephone or video call 6 months after randomization. and every 6 months after the 18-month assessment until the end of the trial, if applicable (Table 2). Study personnel will enter all data collected during assessments directly into our SecuTrial database as described in 2.3.

At every in-person assessment (baseline, 12-, 18-months) we will collect blood and urine samples to determine risk factors, such as LDL HbA1c, and cotinine. Blood and urine samples will be centrifuged, aliquoted and stored at − 80 °C for central analysis before the end of the trial. Samples may be stored for up to ten years and will be disposed of afterwards. Details on the biological specimen handling, storage and shipping are described in our Biological Specimen Handling Manual.

To guide the TC treatment, open assessments of risk factors are performed for intervention patients at baseline and at least once during the intervention period, either by review of routine medical assessments by treating physician(s) or—if no current records are available—by the study center.

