Secondary outcomes are analyzed along the same lines. The count of present dichotomous risk factors over time is analyzed by means of generalized estimating equations (GEE). Moreover, a resampling approach for the analysis of correlated multiple endpoints is taken, e.g. as recently described by Ristl et al. [57]. Time-to-event (e.g., survival) distributions are summarized by the Kaplan–Meier method and compared by the (stratified) log-rank test. Since mortality rates will be low only small survival differences are expected to emerge during the trial. A subgroup analysis will be done by sex (expected male to female ratio about 2:1 [11]). Adverse events will be aggregated by category (e.g., MedDRA) and listed.

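### Adverse events come from blinded assessments in both arms and from care management in TeamCare only; pooling the two sources would bias between-arm counts against TeamCare, and the article does not separate them

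*Protocol article*

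**What the plan says.** The Adverse events section names two routes by which events reach the trial record.

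- **Both arms.** "Our blinded assessors inquire routinely about any adverse events", covering the time since the previous assessment. Follow-up assessments and outcomes gives the timing: "blinded assessors will administer self-report psychometric and medical questionnaires via telephone or video call 6 months after randomization"; "At 12- (end of treatment) and 18-months after randomization participants are invited to come to their recruitment center"; and then "every 6 months after the 18-month assessment until the end of the trial, if applicable". Table 2 agrees, with adverse events and vital status marked at each of these time points.
- **TeamCare only.** "Adverse events reported during care management are also documented". Table 3 assigns care management to TeamCare alone. The Team care intervention section sets its frequency: "During the first 3–4 months of the intervention phase", "NCMs contact patients twice a month for typically" half an hour, and monthly after that unless another interval is indicated. Table 3 also gives the nurses, and only them, the task of screening for suicidal thoughts and unstable cardiac status. Its footnote says that in usual care the physician hears of worsening only if it was seen at a blinded assessment.

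On analysis, the Statistical analysis section has one sentence: "Adverse events will be aggregated by category (e.g., MedDRA) and listed". It does not say whether the two routes are kept apart or merged, and it names no between-arm test of adverse events.

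**The concern.** The two arms are observed with different intensity, and the difference is built into the collection rule. A usual-care patient who has a minor event and forgets it by the next six-monthly interview contributes nothing. A TeamCare patient with the same event may mention it to the nurse within weeks, and it is then documented. If both routes feed one table of counts, nurse reports can only add events, and only in one arm.

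An excess in TeamCare could then not be told apart from better detection. A behavioural programme might look less safe than usual care merely because someone was listening. The primary outcome is not affected.

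**Working it through.** The article gives no adverse event rate and no capture rate, so there is no stated figure to reproduce. The contact counts follow from the text. The size of the bias needs assumptions.

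**1. Contacts in the first 12 months.** With m months of twice-monthly contact followed by monthly contact, the number of nurse contacts is 2m + (12 − m).
- m = 3: 6 + 9 = 15.
- m = 4: 8 + 8 = 16.

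Each arm also has 2 blinded follow-up assessments (months 6 and 12). These counts are not a detection ratio, because each interview covers the whole period since the previous one. Nurse contacts matter only for events that the interviews miss.

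**2. Model with equal true rates.** Let p be the share of events captured by the blinded interviews, the same in both arms. Let q be the chance that an event missed at interview is known from care management. Both are assumptions.
- Usual care records p.
- TeamCare, with sources pooled, records p + (1 − p)q.
- Apparent ratio over 12 months = [p + (1 − p)q] / p.

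| p | q = 0.25 | q = 0.5 | q = 0.8 |
|---|---|---|---|
| 0.6 | 1.17 | 1.33 | 1.53 |
| 0.8 | 1.06 | 1.125 | 1.20 |
| 0.9 | 1.03 | 1.06 | 1.09 |
| 1.0 | 1.00 | 1.00 | 1.00 |

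The ratio is also 1.00 whenever q = 0. It is never below 1.

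**3. Over 18 months.** Nurse contacts stop at month 12, so the ratio is [12(p + (1 − p)q) + 6p] / (18p). For q from 0.25 to 0.8 this gives 1.11 to 1.36 at p = 0.6, 1.04 to 1.13 at p = 0.8, and 1.02 to 1.06 at p = 0.9.

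**4. What this would do to a comparison, if one were made.** Take 220 patients per arm (Sample size calculation), 12 months of complete follow-up, an assumed true rate of 1.0 event per patient-year, Poisson counts and a two-sided 5% Wald test on the log rate ratio. With no bias, the chance of a significant excess against TeamCare is 2.5%.
- p = 0.9, q = 0.25: expected counts 198 (usual care) and 204 (TeamCare); chance about 5%.
- p = 0.8, q = 0.5: 220 × 0.8 = 176 and 220 × 0.9 = 198. ln(198/176) = 0.118, standard error √(1/198 + 1/176) = 0.104, z = 1.14; chance about 20%.
- p = 0.6, q = 0.5: 132 and 176; chance about 70%.

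**5. With the sources separated.** Counting only interview-elicited events gives p/p = 1.00, provided the interviews capture the same share in both arms.

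**The case against.** The strongest objection is that the article never says the sources will be pooled. How adverse events are tabulated is ordinary content for an analysis plan or full protocol, neither of which is shown. The sources also look separable already: nurses enter contact information in the electronic patient registry, and assessors enter theirs in SecuTrial. This stands as a limit on the claim, which is therefore conditional. It does not remove the point, because the unequal collection is stated outright, and the one sentence on analysis describes a single aggregation.

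Several stronger readings are tempting and are not supported.

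- *That TeamCare will look less safe.* This needs pooling and a between-arm comparison, and the article states neither.
- *That the secondary endpoints on medical events and utilisation are contaminated.* Nothing says nurse reports feed any endpoint. The Secondary outcomes section tracks cardiac events and deaths by patient report, discharge notes and death certificates, and says that outcomes are assessed in all participants.
- *That the safety committee's tables are biased.* Their content is governed by a charter that is not shown, so this cannot be checked.
- *That nurses ask about adverse events at every contact.* The text says only that events reported during care management are documented. The active screening it names is limited to the two items in Table 3.
- *That 17-18 opportunities against 2 measures the bias.* The interviews already cover the full period in both arms.

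It is also fair to object to restricting every between-arm summary to interview-elicited events. A patient who has died cannot be interviewed, so deaths would drop out, as would record-confirmed events in patients who miss an assessment. The fix below avoids this.

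**Conclusion.** The point holds in conditional form. Collection is unequal by design. If the two sources are pooled, between-arm adverse event counts would be biased against TeamCare even with no true difference.

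The size cannot be derived from the documents. With interview capture assumed between 60% and 100%, and nurses assumed to pick up none to 80% of what interviews miss, the 12-month ratio runs from 1.00 to about 1.5, and over 18 months from 1.00 to about 1.36. Lower interview capture would push it higher. The bias should be small for deaths, acute coronary syndromes and hospitalisations, which interviews or records should reveal in either arm. It should be larger for milder events and for findings from the TeamCare-only screening.

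This is a cheap improvement to safety reporting and does not threaten the trial's main conclusion.

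**What to change.** In the Adverse events and Statistical analysis sections, or in the analysis plan if it is not already there, state that:

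1. Between-arm adverse event summaries use events elicited by blinded assessors with identical questions in both arms, plus deaths and events confirmed by arm-neutral records (discharge notes, death certificates) obtained by the same procedure in both arms.
2. The source of each event is recorded at entry.
3. Events known only from care management are listed separately, for TeamCare.

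Immediate notification of events of special interest stays unchanged.

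The cost is one source field and a few sentences, and the two existing data systems should make the field easy to fill. The downside is that some milder TeamCare events appear only in the separate listing.

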## Statistical analysis

The primary analysis is based on the intention to treat with no exclusions (full analysis set). The odds of responding to treatment (i.e. ≥ 50% increase in HRQoL from baseline to month 12) are compared between treatment groups (TC vs. UC) by the Mantel–Haenszel test stratified by study site. Heterogeneity of the common odds ratio over strata is evaluated by the Breslow-Day test. A missing response status is counted as failure. Numbers needed to treat are derived from the Mantel–Haenszel odds ratio. Analysis of all subjects who were essentially treated and observed per protocol (PP set) is supportive.

Moreover, the main outcome measure “change in HeartQoL global scale from baseline to month 12” is evaluated by mixed model for repeated measures (MMRM) with fixed effects baseline, study site, treatment, time and the interaction treatment*time (ARH1-structured covariance matrix over time) and estimation of corresponding marginal means and treatment contrasts. It will be expressed in absolute values and in relation to minimal clinically important differences (MCID). The possibly moderating influence of study site, age, sex, disease severity (number of diseased coronary arteries, history of myocardial infarction, CCS and NYHA classes, baseline distress level), and risk factor burden is explored. Since mixed models can be expected to yield valid results only in case of missingness-at-random, multiple imputation approaches are taken to assess the robustness of the results. Specifically, missing values due to death, illness, or chance are separately imputed assuming mixtures of missingness-not-at-random patterns. Imputation data sets are post-processed by multiplication with factors and addition of offsets (tipping point analysis [55]). The influence of clustering of subjects by care providers (particularly in TC) is investigated by multilevel modeling [56].

Secondary outcomes are analyzed along the same lines. The count of present dichotomous risk factors over time is analyzed by means of generalized estimating equations (GEE). Moreover, a resampling approach for the analysis of correlated multiple endpoints is taken, e.g. as recently described by Ristl et al. [57]. Time-to-event (e.g., survival) distributions are summarized by the Kaplan–Meier method and compared by the (stratified) log-rank test. Since mortality rates will be low only small survival differences are expected to emerge during the trial. A subgroup analysis will be done by sex (expected male to female ratio about 2:1 [11]). Adverse events will be aggregated by category (e.g., MedDRA) and listed.

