### Baseline assessment and randomization

All patients eligible for the study are invited to come to the respective recruitment center, where they sign their study consent and complete their baseline assessment. A study physician assesses patients’ detailed medical history, performs a basic medical exam (for details see Additional file 1), and records their prescribed medications (Table 2). Afterwards a study member administers the psychometric assessment. All data are pseudonymized and directly entered into our certified central SecuTrial data base via password-protected tablet computers, that are programmed with skip patterns, drop-down menus, check-off boxes, and error checking routines monitoring forms for out-of-range values and missing data. A data safety plan has been developed for ensuring data protection.

**Table 2 Tab2:** Visit schedule and assessments

Periods	Name	Screen 1 (in-hospital)	*Screen 2* (telephone)	*Randomization*	Treatment		*Follow-up*		
Visits				Baseline Assessment (Visit)	6 months (telephone)	EOT (visit)	FU 18 (visit)	FU 24^a^ (telephone)	FU 30^a^ (telephone)
	Time	Day-120–day-90	Day-14	Day 0	Month 6	Month 12	Month 18	Month 24	Month 30
informed screening consent		X							
Screen 1: Inclusion and exclusion criteria		X							
Screen 2: Inclusion and exclusion criteria			X						
Informed study consent				X					
Demographics				X		X	X		
Medical History^b^				X	X	X	X		
Physical examination^c^				X		X	X		
Laboratory tests^d^				X		X	X		
Psychometric battery 1^e^				X	X	X	X	X	X
Psychometric battery 2^f^				X		X	X		
Medication				X	X	X	X	X	X
Actimetry				X		X	X		
Adverse Events/Vital Status				X	X	X	X	X	X

*EOT* end of study treatment, *FU* follow-up

^a^FU 18 will be administered in all participants to measure treatment durability. FU 24 and FU 30 will only be administered before the end of study, i.e. only in participants included during the first 12 or 6 months, of recruitment, respectively

^b^Full medical history and demographics will be obtained at baseline only. Only relevant changes from baseline will be documented during later assessments

^c^Physical examination will typically be limited to heart rate, blood pressure, body height (baseline only) and weight. Other physical examinations will only be performed based on clinical need

^d^Laboratory tests comprise LDL cholesterol, HbA1c, creatinine, and cotinine

^e^Questionnaires included: HeartQoL (primary outcome), HADS, PSS-4

^f^Questionnaires included: see Table 4

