### Sample size calculation

Katon et al. [11] observed in their TeamCare Trial proportions for the response to treatment of 60% (intervention group) and 30% (control group), respectively, for ≥ 50% decrease in depression score. Thus, assuming a ≥ 50% increase in HRQoL on the HeartQoL score, we expect response proportions of 50% (TC) and 35% (UC), i.e. a difference of 15% absolute. The chi-square test requires 170 subjects per group to detect this difference with a power of 80% and a two-sided type-I-error of 5% (Stata/SE 16.1, StataCorp LLC, College Station, TX, USA). Similar to Katon et al. [11] we expect a standardized effect of at least 0.3 in favor of TC. The two-sample *t*-test requires 176 subjects per group to reach an 80% power at a two-sided type-I-error of 5%. Accounting for 15% attrition and (partial) therapist clustering [56] in TC (+ 5%), 220 (≈176/0.8) patients need to get randomized per group, i.e. 440 subjects in total. Adjusting for baseline in a mixed model for repeated measures (MMRM) approach is likely to further increase the statistical power.

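### The primary responder test is valid but adjusts for site only; prespecifying adjustment for baseline HeartQoL would be a cheap improvement

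*Protocol article*

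**What the plan says.** All references are to the protocol article.

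- **Primary test (Statistical analysis).** The odds of response "are compared between treatment groups (TC vs. UC) by the Mantel–Haenszel test stratified by study site". A missing response counts as failure, and the number needed to treat is derived from the Mantel–Haenszel odds ratio.
- **Endpoint (Primary outcome).** Response is the share of the possible gain that was achieved: "score_12 months_-score_baseline_)/(3-score_baseline_) ≥ 50" per cent.
- **Baseline is measured (Table 2, note on psychometric battery 1).** "Questionnaires included: HeartQoL (primary outcome), HADS, PSS-4"; this battery is scheduled at the baseline visit.
- **Where baseline is a covariate (Statistical analysis).** Only in the further mixed model of HeartQoL change, "with fixed effects baseline, study site, treatment, time and the interaction treatment*time".
- **Randomization.** 1:1, stratified by study site and nothing else.
- **Sample size calculation.** "we expect response proportions of 50% (TC) and 35% (UC), i.e. a difference of 15% absolute", with an unadjusted chi-square test. The section closes with a remark on the mixed model: "Adjusting for baseline in a mixed model for repeated measures (MMRM) approach is likely to further increase the statistical power".

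**The concern.** The confirmatory conclusion rests on one test. That test does not use the covariate most closely tied to its endpoint, although the trial collects it and uses it in the mixed model of the same scale.

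Having baseline in the endpoint formula is not the same as adjusting for it. The formula removes the dependence on baseline only at one particular slope of month-12 score on baseline. At any other slope, two things follow. Some power is lost that could be had without new data. And because randomization is stratified by site alone, a chance difference in baseline HeartQoL between the arms carries through to the primary result. An adjustment chosen after such a difference has been seen would be post hoc.

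**Working it through.** **1. The plan's own figures.** For 50% vs 35%, two-sided 5%, 80% power, pooled variance:

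n = [1.96·√(2·0.425·0.575) + 0.8416·√(0.5·0.5 + 0.35·0.65)]² / 0.15² = (1.370 + 0.582)² / 0.0225 ≈ 169.3, so 170 per group, as stated. The t-test figure of 176 and 176/0.8 = 220 also reproduce. None of these relies on baseline adjustment.

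**2. What response means.** For a baseline b below 3, (M12 − b)/(3 − b) ≥ 0.5 is the same as M12 ≥ b + (3 − b)/2 = (3 + b)/2. Response therefore depends on D = M12 − 0.5·b.

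**3. When baseline predicts response.** Assume equal SDs at both times and no ceiling. Then Cov(b, D) is proportional to r − 0.5 and Var(D) to 1.25 − r, so corr(b, D) = (r − 0.5)/√(1.25 − r).

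| r | corr(b, D) | squared |
|---|---|---|
| 0.2 | −0.29 | 0.09 |
| 0.4 | −0.11 | 0.01 |
| 0.5 | 0 | 0 |
| 0.6 | 0.12 | 0.02 |
| 0.7 | 0.27 | 0.07 |
| 0.8 | 0.45 | 0.20 |

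The association vanishes at r = 0.5 and grows on either side. Dichotomising weakens it: in simulation (baseline mean 1.5, SD 0.6) baseline explained about 5% of the responder variance at r = 0.2, 0% at 0.5, 4–5% at 0.7 and 12% at 0.8.

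**4. Power at the planned size.** With 220 analysed per group the unadjusted test has 89.2% power. If the plan's 15% attrition falls equally on both arms and counts as failure, the rates become 0.85·50% = 42.5% and 0.85·35% = 29.75%, and power is 79.7%, before any therapist clustering. If baseline explains a share R² of the responder variance, n acts like n/(1 − R²). Power then becomes 80.5%, 81.7% and 83.7% for R² = 0.02, 0.05 and 0.10.

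**5. Simulation.** 440 patients, six sites, 50% vs 35% before missingness, 15% missing counted as failure, 3,000 runs per setting. Site-only Mantel–Haenszel is compared with the score test for treatment in a logistic regression on site, baseline and baseline squared. HeartQoL moments are assumptions (baseline mean / baseline SD / month-12 SD): A = 1.5/0.6/0.6, B = 1.8/0.6/0.7.

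| r | A: site only → adjusted | B: site only → adjusted |
|---|---|---|
| 0.2 | 78.6 → 80.8% | 81.0 → 82.8% |
| 0.5 | 78.4 → 79.4% | 79.7 → 80.2% |
| 0.7 | 79.7 → 81.6% | 79.5 → 82.5% |
| 0.8 | 79.4 → 83.8% | 80.6 → 85.5% |

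Power was not lower after adjustment in any of 14 settings. Null rejection was 4.9–5.9% adjusted and 4.7–5.8% for Mantel–Haenszel.

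Part of the gain near r = 0.5 is not due to baseline. With 440/6 ≈ 73 patients per site, the Mantel–Haenszel variance carries a factor n/(n − 1) = 73.3/72.3 ≈ 1.014. At 80% power that is worth Φ(2.8016·√1.014 − 1.96) ≈ 80.5%, about half a point.

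A separate simulation of the same design gave 79–80% vs 80% at r = 0.3–0.5, 79–80% vs 81–83% at 0.7, and 80–82% vs 85% at 0.8. A third, without missing data and with baseline entered linearly (220 per group, 1,500 runs, Monte Carlo error about 0.8–1 point), gave 88.6 vs 89.1% at 0.5, 89.3 vs 91.1% at 0.7 and 87.9 vs 92.0% at 0.8.

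**6. Chance imbalance.** The standard error of the baseline difference is √(2/220) = 0.095 SD. A difference above 0.15 SD (0.15/0.095 ≈ 1.57) therefore occurs in roughly one trial in ten. In such null trials the mean Mantel–Haenszel z shifted by about 0.4–0.5 at r = 0.7 and 0.5–0.7 at r = 0.8. The adjusted z stayed near zero (largest shift 0.22, from few trials).

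**7. Finer stratification is no substitute.** Without missing data, Mantel–Haenszel by site and baseline tertile (18 strata) gave 88.2% vs 88.9% for site only at r = 0.2, 87.9 vs 88.6% at 0.5, and 90.9 vs 87.9% at 0.8.

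**The case against.** The case for leaving the test alone is strong in several respects.

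- **The test is valid.** It stratifies by the only randomization stratum and fits the sample-size calculation. Randomization protects the type I error whether or not baseline is a covariate. This stands, so nothing here is an error.
- **A reader might infer that the protocol contradicts itself,** by crediting baseline adjustment with power and then leaving it out of the primary test. The closing sentence of the sample-size section concerns the mixed model of the continuous score only. The protocol makes no such statement about the responder test.
- **A reader might infer that baseline is ignored.** It is not: it enters the responder formula, and a baseline-adjusted mixed model of the same scale is prespecified. But the formula is not an adjustment except at a slope of 0.5, and the mixed model does not correct the confirmatory result.
- **The gain is small over much of the plausible range,** and the largest gain needs r = 0.8, which nothing in the document supports. This stands and limits the weight of the point.
- **Enrolment began in November 2020.** Changing a confirmatory test needs care, but it is legitimate before unblinding and needs no new data.

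The statistical analysis plan was not available here and may already contain a baseline-adjusted responder analysis. The article does, however, fix the primary test.

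**Conclusion.** The point holds as a cheap improvement. The site-only Mantel–Haenszel test is valid, but it does not use a covariate that predicts response whenever the slope of month-12 on baseline score differs from 0.5.

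Over the assumed range, adjustment adds about 0–1 point of power near r = 0.5, about 2–4 points at r = 0.7 and about 4–5 points at r = 0.8. It kept type I error at about 5% and did not cost power in any setting examined. It also removes most of the effect of chance imbalance in baseline HeartQoL.

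These sizes rest on assumed HeartQoL means, SDs and correlations, because the article gives none. They also assume 15% missing in both arms, counted as failure, and no therapist clustering. A definite loss of power cannot be claimed from the document.

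**What to change.** Before unblinding, prespecify as the primary test the treatment term of a logistic regression with site and baseline HeartQoL, with the functional form of baseline fixed in advance. Report the standardised (marginal) risk difference with its confidence interval and derive the number needed to treat from it. That avoids converting an odds ratio through an assumed control risk. Keep the site-stratified Mantel–Haenszel test as a sensitivity analysis. If the sponsor prefers to keep it as primary, the adjusted analysis should at least be prespecified as supportive.

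The cost is wording, with no new data. The adjusted odds ratio is conditional on baseline and so is not the quantity the Mantel–Haenszel test estimates, which is why the marginal risk difference belongs beside it. The statements on the Breslow–Day test and on the number needed to treat, both tied to the Mantel–Haenszel odds ratio, need rewording.
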